### Sample Size and Sampling

The minimum sample size was calculated according to the stages of data collection in the pretest and posttest. To evaluate the responsiveness of part 1 of the RRT survey comparing the scores from the two evaluation periods, a paired student *t* test was used. In this calculation, a significance level of 5% was assumed with a test power of 80% and an effect size of 0.50, which, according to Cohen [17], can be considered an effect size of medium degree. The calculation resulted in a minimum sample of 34 participants. To carry out this sample calculation, G*Power 3.1.9.2 software was used [18,19].

To assess the internal consistency of part 2 of the RRT survey, we referred to the recommendation proposed by the COSMIN (Consensus-Based Standards for the Selection of Health Measurement Instruments) initiative that at least 50 participants are necessary for a sample to be considered adequate when this measurement property is evaluated [20].

To evaluate assertiveness in filling out the NEWS2 before and after the intervention, the same methodology was proposed by the COSMIN initiative that at least 50 participants are necessary [20]. Thus, 50 participants will be included in the study to meet all the proposed objectives.

### Recruitment

The human resources records of each eligible participant will be accessed through a list of registered nurses in floor units. Participants who engage in the study will be scheduled for a baseline appointment. On the appointed day, the interviewer will personally invite the participant and both will sign two copies of the research consent form.

### Randomization and Allocation Concealment

Considering the nature of a JITT, no randomization will be conceived. All nurses allocated in floor units will be sequentially included according to their availability, schedule, and willingness to participate.

### Implementation

The lead investigator will implement intervention strategies.

### Blinding

This is not a blind study as both the lead investigator and participants will know they are receiving an intervention.

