#### Preintervention Assessment

In this step, a questionnaire [15] will be used to assess the theoretical content related to each participating nurse’s early assessment of clinical deterioration to compare the pretraining and posttraining results. The Brazilian version of the rapid response team (RRT) survey, which aims to explore nurses’ knowledge and perceptions of RRTs, was translated and adapted into Brazilian Portuguese and validated ([name] and [name], unpublished data). This instrument has 3 parts: part 1 contains 4 hypothetical case studies; in part 2, respondents must evaluate each factor according to its degree of importance; and in part 3, participants must include their basic information regarding characteristics and work history.

Although this tool has been widely used globally, no studies have been published on its psychometric properties. Assessing the psychometric properties of a measurement tool is relevant for ensuring its validity, reliability, and suitability for data collection in most research contexts. However, there are situations where a psychometric evaluation may be unnecessary, such as for well-established and widely used tools, especially those that do not measure psychosocial constructs (eg, the RRT survey). Once the tool has been extensively used, widely accepted, and has a solid empirical foundation in the literature, conducting a full psychometric assessment may not be necessary [16].

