### Data Collection

The experiment will be offered from July to December 2023 and include nurses who work in the clinical and surgical floor units.

Initially, a meeting will be held with the managers of the inpatient units to present the training program. Then, nurses will be recruited through an individual invitation to be offered by the researcher in the work units. After acceptance by the participants, a roster will be set up, together with the managers of the units, to assist in the organization of work rosters so that every position is covered when the nurses leave to participate in the training. Several training sessions will be made available in the morning, afternoon, and evening to carry out the training within the working hours of each nurse and according to what was described in the JITT method. The training sessions are structured to be 1 hour long and include the following steps: training presentation, signing of the informed consent form, application of the pretest, training, application of the posttest, and final evaluation. All nurses will participate in a single session and receive a participation certificate after completing all the steps described. The training will be carried out in a training room within the hospital.

Content analysis will be carried out during the qualitative phase (focal group). The most appropriate contents and strategies for nurses, as defined by them, will be combined to determine the elements of the intervention. Regarding the web-based questionnaire and the RRT survey, both of which are quantitative instruments, any increase in the score from the pretest to posttest will represent an improvement and, consequently, indicate the effectiveness of the intervention.

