### Data Management

The gathered data will be compiled in a spreadsheet using Excel 2010 (Microsoft Corporation) using double entry. In this spreadsheet, numerical encodings will be created for categorical variables. Quantitative variables will be inserted as collected. To avoid erroneous double entries or differences in the created codes, preset values for categorical variables will be used. The spreadsheet containing the data will be password-protected and solely accessible by the lead investigator.

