### Data Analysis

The data spreadsheet will be imported into SAS 9.4 software (SAS Institute). The results of the focus groups, as well as the preintervention and postintervention assessment questionnaires, will be submitted for content analysis.

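### The stated reason for not blinding covers delivery of the training only; completed forms could be scored masked to time point, and the article leaves unsettled whether they are scored by key or by judgement

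*Protocol article*

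**What the plan says.** Five statements in the Methods of the protocol article bear on this point.

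- **Blinding:** "This is not a blind study as both the lead investigator and participants will know they are receiving an intervention". No other reason is given, and scorers, coders and the analyst are not mentioned.
- **Implementation:** "The lead investigator will implement intervention strategies".
- **Data Management:** "The spreadsheet containing the data will be password-protected and solely accessible by the lead investigator". The same section also provides for double entry and preset values for categorical variables.
- **Data Analysis:** the focus-group results, "as well as the preintervention and postintervention assessment questionnaires, will be submitted for content analysis".
- **Data Collection:** content analysis is placed in the focus-group phase. The web-based questionnaire and the RRT survey are described differently: "both of which are quantitative instruments, any increase in the score from the pretest to posttest will represent an improvement".

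Preintervention Assessment adds that, in the RRT survey, "part 1 contains 4 hypothetical case studies". Statistical Analysis compares the NEWS2 score and the RRT part 1 score between the two time periods by paired t or Wilcoxon tests.

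**The concern.** Knowing that training is being given is a property of the trainer and the trainee. It says nothing about whoever later scores a completed form, who can be kept unaware of whether that form was filled in before or after the session. The Blinding section therefore gives up a protection that its own reason does not rule out.

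This matters more here than in a controlled trial. Trial Design and Settings describes a single-arm before-and-after study intended to show causality, so the time-point label is the whole comparison. Any tendency to read after-training answers more generously goes straight into the estimated effect, with no control arm in which it would cancel. Data Collection also counts any rise in score as evidence of effectiveness, with no minimum margin, so even a small scoring shift could count in favour of the training.

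Whether there is room for such a shift depends on how forms are scored, and on that the article gives two answers.

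**Working it through.** **Step 1. Set the passages side by side.**

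| Question | Where | Answer in the article |
|---|---|---|
| Why is the study not blind? | Blinding | Lead investigator and participants know of the training |
| Who delivers the training? | Implementation | Lead investigator |
| Who can access the data? | Data Management | Lead investigator only |
| How are the pre and post questionnaires handled? | Data Analysis | Content analysis |
| How are they handled? | Data Collection, Statistical Analysis | As quantitative scores, compared by paired tests |
| Is the scorer masked to time point? | Nowhere | No masking described |

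The questionnaire used before and after training is the RRT survey (Preintervention and Postintervention Assessment). Data Analysis and Data Collection therefore give the same instrument two treatments: coding by judgement, or a numerical score. They cannot both describe how part 1 is scored.

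**Step 2. Reproduce the plan's own figure.** Sample Size and Sampling gives a 5% significance level, 80% power, effect size 0.50 and a paired t test, with a minimum of 34. Power of the two-sided paired t test is

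P(|T| > t(0.975, n − 1)), with T noncentral t on n − 1 degrees of freedom and noncentrality d × √n.

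- n = 33, d = 0.50: 0.795
- n = 34, d = 0.50: 0.808

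The smallest n reaching 0.80 is 34, as stated. The article does not give the sidedness; a one-sided test would need only 27, so the stated figure is two-sided. At the planned 50 nurses, power at d = 0.50 is 0.934.

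**Step 3. Put a scoring shift into the same formula.** Let the true training effect be zero, and let after-training forms be scored higher by b, in SD of the paired difference. The noncentrality becomes b × √n. The article gives no value for b, so the range is an assumption.

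| b (assumed) | b × √50 | Chance of a significant result, n = 50 | Same, n = 34 |
|---|---|---|---|
| 0 (fixed key) | 0 | 0.050 | 0.050 |
| 0.05 | 0.35 | 0.064 | 0.059 |
| 0.1 | 0.71 | 0.107 | 0.087 |
| 0.2 | 1.41 | 0.284 | 0.205 |
| 0.3 | 2.12 | 0.548 | 0.397 |

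The n = 50 column is the relevant one, since 50 is the planned sample. If there is a true effect d, the expected estimate is d + b. A shift of 0.2 is 0.2 / 0.50 = 40% of the effect size the study was planned on.

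**The case against.** **The article never says who scores the forms.** A reader might infer that the lead investigator judges each form knowing whether it came before or after the training. The documents do not support that. Implementation names who delivers the training, and Data Management restricts access to a spreadsheet; neither assigns scoring. No section says that the time point is visible to the scorer. This objection stands, and the point is limited accordingly: the trainer is sole data holder, and no masking is described.

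**A condensed article may leave the scorer and the key to fuller documents.** This also stands, and the absence of a key is not the point. The point rests on what is printed: a reason for not blinding that does not reach scoring, and two sections that disagree on how the questionnaires are analysed.

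**Most of the text points to numerical scoring.** Data Collection and Statistical Analysis treat the instruments as scores, and double entry and preset values guard against entry errors. If part 1 has a fixed key, the shift is close to zero. That is a fair limit on the size. It does not remove the content-analysis sentence, and double entry does not protect a score that was judged before entry.

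**Free-text answers and judged NEWS2 sheets are not documented.** A reader might assume both. The article gives no answer format for the four cases and speaks only of NEWS2 completion and score, so neither assumption should be relied on.

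**The percentages are generic.** They would apply to any shift in a paired study of 50. They show what a shift would do, not that one exists.

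**Conclusion.** The point holds as an inexpensive improvement. The reason given for an unblinded study justifies open delivery but not open scoring, the person who delivers the training alone holds the data, and the article contradicts itself on whether the pre and post questionnaires are scored or coded by judgement.

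The size is conditional. With no true effect and an assumed shift of 0 to 0.3 SD of the paired difference, the false-positive chance at 50 nurses runs from 5% to 55%. The low end applies if a fixed key is used; the upper values require judgement in scoring and a scorer aware of the time point, neither of which the article establishes. It would be wrong to conclude that the result will be biased, or that the plan prescribes scoring with the time point known. What can be said is that the described procedures do not prevent it.

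**What to change.** 1. Amend Blinding to say that delivery is open and scoring is masked to time point.
2. Reconcile Data Analysis with Data Collection: keep content analysis for the focus groups, and score RRT part 1 and NEWS2 by a key fixed before the first session.
3. Label each form with a random code that hides nurse and time point. A member of the existing team who does not score should hold the code list; the focus-group presentation box mentions a team of three nurses.
4. Score all pre and post forms together, in random order, after the last session.
5. Link codes to time points only once the scores are locked.
6. Adjust the sole-access rule in Data Management to match. If the lead investigator both scores and holds the code list, the masking is nominal.

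The cost is a short amendment and coding of 50 × 2 = 100 sets of forms. Sample size, instruments and delivery are unchanged, and no staff are added. The drawbacks are that scoring waits until sessions end and that masking may be imperfect where an answer itself reveals training. Bias from unblinded participants, and from retesting within the same 1-hour session, is not removed and should be acknowledged under Limitations.

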### Data Collection

The experiment will be offered from July to December 2023 and include nurses who work in the clinical and surgical floor units.

Initially, a meeting will be held with the managers of the inpatient units to present the training program. Then, nurses will be recruited through an individual invitation to be offered by the researcher in the work units. After acceptance by the participants, a roster will be set up, together with the managers of the units, to assist in the organization of work rosters so that every position is covered when the nurses leave to participate in the training. Several training sessions will be made available in the morning, afternoon, and evening to carry out the training within the working hours of each nurse and according to what was described in the JITT method. The training sessions are structured to be 1 hour long and include the following steps: training presentation, signing of the informed consent form, application of the pretest, training, application of the posttest, and final evaluation. All nurses will participate in a single session and receive a participation certificate after completing all the steps described. The training will be carried out in a training room within the hospital.

Content analysis will be carried out during the qualitative phase (focal group). The most appropriate contents and strategies for nurses, as defined by them, will be combined to determine the elements of the intervention. Regarding the web-based questionnaire and the RRT survey, both of which are quantitative instruments, any increase in the score from the pretest to posttest will represent an improvement and, consequently, indicate the effectiveness of the intervention.

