### Trial Design and Settings

A quasi-experimental study of the type before and after, with a single arm, will be conducted with all nurses from inpatient units of a tertiary-level university hospital in the interior of the southeast of São Paulo to implement a training program to assess the risk of early clinical deterioration. This study aims to demonstrate causality between the proposed intervention and the nurses’ ability to use the NEWS2 tool to assess the patient’s clinical deterioration and provide appropriate referrals. Quasi-experimental designs are often used when assigning participants randomly to different groups is not feasible or ethical. This allows for intragroup comparison of outcomes (ie, comparing the pretraining and posttraining results in the same group). In this study, having only a subset of the staff receiving the training would not be feasible. Although a quasi-experimental design does not offer the same level of control as a randomized controlled trial, it can provide valuable insights into the effects of the training program because it offers a real-world evaluation of the intervention’s impact within the specific setting and considers the practical constraints of implementation.

The trial was registered in the Brazilian Registry of Clinical Trials (ReBEC) with the number RBR-5hq9y3k. For the design of the method, the limits of the Guideline for Reporting Evidence-Based Practice Educational Interventions and Teaching (GREET) [11] were respected.

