#### Postintervention Assessment

In this step, the Brazilian version of the RRT survey will be reapplied to compare the pretraining and posttraining results and evaluate the effectiveness of the intervention.

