### Limitations

Some limitations pertaining to the study’s design and methodology exist. The limited generalizability is a concern, as the study will be conducted in a specific public university hospital in southeastern Brazil, potentially limiting the applicability of the findings to other health care settings or regions. Potential selection bias is another limitation, as the recruitment process will not be randomized. The data collection period may restrict the gathering of a comprehensive and long-term data set.

The second set of limitations revolves around data collection and analysis. The qualitative stage involving focus groups and interviews with nurses introduces the possibility of self-reporting bias, where participants may provide socially desirable responses, or their recollections may not accurately reflect their actual practices. Finally, it is not possible to control or account for potential confounding factors, such as patient demographics or other interventions that may influence the outcomes.

Despite the acknowledged limitations, this paper provides a valuable contribution by outlining the design of a nurse-led intervention program that other health care professionals can replicate. The structured and systematically mapped intervention presented in this study offers the potential for improved resource allocation and results optimization. By enhancing nurses’ ability to detect early signs of clinical deterioration and facilitating prompt and accurate interventions, this program holds promise for improving patient outcomes and increasing the likelihood of positive treatment outcomes.

Some studies have demonstrated the effectiveness of using intervention mapping in nursing in planning and implementing interventions and evaluating results. The research subjects reported that the interventions allowed a better understanding of the studied models [27,28].

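### The study sets out to demonstrate causality and reads any score rise as effectiveness, but an uncontrolled repeat of the same survey within one hour cannot separate training from testing effects

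*Protocol article*

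**What the plan says.** All statements are in the protocol article.

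- **Aim and design (Trial Design and Settings).** The design is given as "A quasi-experimental study of the type before and after, with a single arm". The same paragraph states: "This study aims to demonstrate causality between the proposed intervention and the nurses"' ability to use NEWS2 and refer appropriately. It concedes less control than a randomized trial and says that training only part of the staff would not be feasible.
- **Allocation (Randomization and Allocation Concealment).** "no randomization will be conceived"; nurses enter sequentially as they are available and willing.
- **Instrument (Preintervention and Postintervention Assessment).** Part 1 of the RRT survey has four hypothetical cases. After training, "the Brazilian version of the RRT survey will be reapplied to compare the pretraining and posttraining results and evaluate the effectiveness of the intervention".
- **Timing (Data Collection).** The session lasts 1 hour and consists of "training presentation, signing of the informed consent form, application of the pretest, training, application of the posttest, and final evaluation". Each nurse attends one session.
- **Interpretation (Data Collection).** Any rise in score between the two tests is to count as improvement and hence as effectiveness.
- **Analysis (Statistical Analysis).** NEWS2 and RRT part 1 scores at the two times are compared by paired t or paired Wilcoxon test, at the 5% level.
- **Limitations.** These cover generalizability, selection, a restricted data collection period, self-report in the qualitative stage, and the statement that "it is not possible to control or account for potential confounding factors", with patient demographics and other interventions as examples. Testing and recall effects are not named.

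**The concern.** The second administration follows the first within the hour, with the same four cases, given to nurses who know they have just been trained. Scores could rise because the cases are now familiar, because the material was heard minutes ago, or because participants see what is expected of them. None of these is the lasting ability to recognise deterioration and refer, which is what the causal aim refers to.

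These effects mostly push scores up, so the bias favours a conclusion that the training works. The any-increase rule makes this worse, because it asks for no test, interval or minimum size. At stake is whether the study can support the claim it says it will make.

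**Working it through.** **1. The plan's own figure.** Sample Size and Sampling gives a 5% level, 80% power, effect size 0.50, paired t test, and a minimum of 34. Taking 0.50 as the mean difference divided by the SD of the paired differences (d), power for a two-sided test is

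P(|T| > t(0.975, n − 1)), where T is noncentral t with n − 1 degrees of freedom and noncentrality d√n.

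- n = 33: power 0.795
- n = 34: power 0.808
- n = 50 (planned): power 0.934

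The stated 34 is reproduced, so the sample size is right for the test named. The problem lies in what that test can show.

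**2. What the measured change contains.** For each nurse, post minus pre = training effect + testing effect (case familiarity, recall, demand) + error. Separating the first two terms needs at least one of the following:

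| Source of information | In the article? |
|---|---|
| Untrained nurses tested twice | No; single arm |
| Different cases at the second test | No; the survey is reapplied |
| Second measurement before training | None described |
| Later measurement, when recall has faded | None described; one session per nurse |

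Every participant has two scores with the training between them. No analysis of those two scores can divide the sum into its parts, so this is not a detail that a statistical analysis plan could settle.

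**3. Illustrative size.** The documents give no testing effect, so a range is assumed. Set the training effect to zero and let the testing effect be b, in SDs of the paired difference. The same formula applies with d = b. At n = 50 the critical value is 2.01.

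| b | b√50 | P(significant), n = 50 | P(significant), n = 34 |
|---|---|---|---|
| 0 | 0 | 0.050 | 0.050 |
| 0.1 | 0.71 | 0.107 | 0.087 |
| 0.2 | 1.41 | 0.284 | 0.205 |
| 0.3 | 2.12 | 0.548 | 0.397 |

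For b above zero nearly all these rejections favour the training (at n = 50: 0.103, 0.283 and 0.548). A larger sample raises the probability and does not remove the bias.

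**4. The any-increase rule.** Applied to the mean score, it is met with probability Φ(b√n). At n = 50 this is 0.50 for b = 0, 0.92 for b = 0.2 and 0.98 for b = 0.3. A session with no effect of any kind would satisfy it about half the time.

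**5. Sensitivity to the scale.** If the shift is expressed in SDs of the score and not of the difference, then d = shift/√(2(1 − ρ)), where ρ is the pre-post correlation (not given). A shift of 0.2 score SD at n = 50 gives:

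- ρ = 0.2: d = 0.158, probability about 0.19
- ρ = 0.5: d = 0.200, probability 0.28
- ρ = 0.8: d = 0.316, probability 0.59

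**The case against.** A single-arm before-after design is legitimate, the article gives a feasibility reason for it, and it admits the loss of control. It concedes that confounding cannot be dealt with and that the collection period limits long-term data, and it never claims retention. On this view only an overstated sentence remains.

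Much of that stands. The single arm is not an error, and the absence of a delayed test is a design choice. What does not stand is that the listed limitations cover the problem: the examples given for confounding are patient demographics and other interventions, and testing effects arise from the measurement schedule itself. Nor does admitting less control fit with an aim to demonstrate causality or with the any-increase rule.

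Three stronger readings are tempting but not supported:

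- *That 11%, 28% and 55% are this trial's false-positive rates.* They rest on an assumed shift and on the SD chosen; the documents give neither a shift nor a correlation.
- *That a delayed test must become the main effectiveness time point.* An uncontrolled later test brings its own problems, such as intervening events and contact between colleagues. The bar on other training applies only during the intervention.
- *That testing at the baseline appointment and subtracting the change would remove the bias.* The Recruitment section has consent signed at that appointment, while Data Collection has it signed in the session, so the two may be one occasion. Even if they are separate, practice over a longer gap need not equal practice over minutes.

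It is also an inference that the trainer is present at the posttest. The article says who implements the intervention, not who administers the survey.

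**Conclusion.** The point holds as a mismatch between claim and design. The planned data can estimate an immediate, uncontrolled pre-post change; they cannot show that the training caused it, and a rise in score does not establish effectiveness. The likely direction of bias is towards effectiveness. Its size is unknown from the documents. The probabilities of about 11%, 28% and 55% show only that modest testing effects (0.1 to 0.3 SD of the paired difference, assumed, with zero training effect and n = 50) would often produce a significant result. The conclusion itself does not depend on those figures: it follows from the session sequence, the reuse of the survey and the lack of any comparison. The sample size calculation is not in question.

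**What to change.** Required, at the cost of wording only:

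1. **Trial Design and Settings.** Replace the causal aim with: *to estimate the uncontrolled, same-session pre-post change in RRT part 1 and NEWS2 completion scores*. Limit the conclusion to that. NEWS2 must stay in the sentence, because the sample size and statistical analysis sections both plan that comparison.
2. **Data Collection.** Delete the rule that any increase indicates effectiveness. Report the mean paired change with its 95% confidence interval and the test already planned, described as an immediate change that includes any testing effect.
3. **Limitations.** Name testing and recall effects, and the lack of retention data.

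Optional:

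- Repeat RRT part 1 on the web some weeks after the session as a secondary measure. This costs one extra short survey per nurse and some non-response.
- Add a second administration before training. This is a further extra survey, feasible only if the baseline appointment is separate from the session, which the article should clarify. It would indicate the practice effect only roughly and should not be used as an exact correction.

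Under either option every nurse is still trained.

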#### Assessment of Suitability, Acceptability, and Quality of the Intervention

The nurses’ assessment regarding the suitability, acceptability, and quality of the proposed intervention will be assessed through a self-answered, open-questions questionnaire. This questionnaire will have its content submitted for validation by specialists.

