### Statistical Analysis

Qualitative variables will be described by calculating frequencies and percentages, and quantitative variables through position measurements and dispersion.

Comparisons between the two time periods concerning the score of the NEWS2 instrument and part 1 of the RRT survey instrument will be carried out using paired Student *t* tests or paired Wilcoxon tests [21], according to the data distribution. The distribution of data will be evaluated using the Shapiro-Wilk test.

The internal consistency of part 2 of the RRT survey instrument will be assessed using Cronbach α coefficient [22]. This coefficient ranges from 0 to 1, where values >.7 indicate that the measurements are reliable [23].

The statistical software SAS and SPSS (version 28; IBM Corp) will be used to carry out the analysis with a significance level of 5%.

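### The effectiveness rule covers the whole RRT survey and an unidentified web-based questionnaire, while the planned comparisons cover only RRT part 1 and NEWS2

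*Protocol article*

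**What the plan says.** The protocol article says what counts as success in two places and what will be compared in a third.

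- **Data Collection** sets the rule. It opens "Regarding the web-based questionnaire and the RRT survey, both of which are quantitative instruments" and continues that "any increase in the score from the pretest to posttest will represent an improvement and, consequently, indicate the effectiveness of the intervention". No part of the survey is singled out, and NEWS2 is not named.
- **Postintervention Assessment** also refers to the survey without restriction: "the Brazilian version of the RRT survey will be reapplied to compare the pretraining and posttraining results and evaluate the effectiveness of the intervention".
- **Preintervention Assessment** describes three unlike parts. The first is a set of four invented cases, and the last records the nurse's own background and employment. Of the middle one the article says that "in part 2, respondents must evaluate each factor according to its degree of importance".
- **Statistical Analysis** is narrower. The paired tests are for "Comparisons between the two time periods concerning the score of the NEWS2 instrument and part 1 of the RRT survey instrument". Part 2 appears there only for Cronbach's alpha. Sample Size and Sampling follows the same split: the paired calculation is for part 1, and part 2 is considered only for internal consistency.

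The web-based questionnaire is named only under Data Collection. A separate form on suitability, acceptability and quality "will be assessed through a self-answered, open-questions questionnaire", but the article does not say that the two are the same.

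**The concern.** A rule that reads every increase as benefit needs a score on which higher is better. Part 1, the case studies, can be such a score once its key and direction are fixed. Part 2 asks how important the nurse considers each factor, and the article nowhere says that a higher rating is a better answer. Yet the rule, as worded, takes in the whole survey.

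The design makes this matter. There is one unblinded arm, and pretest, training and posttest all fall within a single one-hour session. Nurses who have just been taught the topic may well rate its factors as more important without having learned to judge cases better. Under the literal rule that shift could be presented as effectiveness, although no test of it is planned. At the same time the rule leaves out NEWS2, which is compared in the analysis and is central to the aim given under Trial Design and Settings.

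**Working it through.** **1. Rule and analysis side by side**

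| Component | How the article describes it | Covered by the success rule | Planned pre-post test |
|---|---|---|---|
| RRT part 1 | 4 hypothetical cases | Yes, as part of the survey | Yes |
| RRT part 2 | Importance ratings | Yes, as part of the survey | No; Cronbach's alpha only |
| RRT part 3 | Characteristics and work history | Nominally; no score is described | No |
| NEWS2 | Score on completing the tool | Not named | Yes |
| Web-based questionnaire | Not described | Yes | Not named |

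Rule and analysis agree on one row, RRT part 1. Part 2 is the row of practical consequence: it consists of ratings, so a score could be formed from it, the rule would read a rise as benefit, and no comparison is planned.

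A further statement, under Data Analysis, sends the pre- and postintervention questionnaires to content analysis. This does not fit the description of the instruments as quantitative, and it does not help to identify the web-based questionnaire.

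**2. The plan's own figure**

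Inputs from Sample Size and Sampling: paired t test on part 1, significance level 0.05, power 0.80, effect size 0.50, stated minimum 34. Sidedness is not stated.

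Two-sided power is the probability that a noncentral t variable, with n − 1 degrees of freedom and noncentrality 0.50 × √n, falls beyond the two-sided 5% critical values.

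- The smallest n that reaches 0.80 is 34. Noncentrality is 0.50 × √34 = 2.92 and power is 0.808.
- A one-sided test would need 27, so the stated figure is the two-sided calculation.
- At the planned 50 participants, noncentrality is 0.50 × √50 = 3.54 and power is 0.934.

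The figure of 34 reproduces, and it concerns part 1 alone. Narrowing the rule to the tested endpoints leaves it unchanged.

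**3. What the literal rule does without a test**

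Assume no true effect and a continuous change distributed symmetrically about zero.

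- Chance that the mean score rises: 0.50.
- Chance that the planned two-sided 5% test is significant in the favourable direction: 0.05 / 2 = 0.025.
- If part 1 and part 2 each gave a score and their changes were independent, the chance of at least one rise would be 1 − 0.50² = 0.75.

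The last two assumptions (a part 2 score and independence) are not in the article. The figures illustrate the wording and are not predictions for this trial.

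**The case against.** The strongest reply is that the analysis sections already settle the matter. The paired comparison and the sample size are both tied to part 1, part 2 is given only a reliability coefficient, and no section plans a before-and-after comparison of part 2 or part 3. On that view, the score in the Data Collection sentence simply means the one RRT score that the protocol compares.

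Much of this stands, and it rules out several stronger readings that a reader might infer:

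- *That the trial will test part 2 or part 3 changes as benefit.* No such test is planned, and no score is described for part 3.
- *That part 2 could swamp or cancel a gain in part 1.* This needs an RRT total. None is defined, and the parts are handled separately. The article gives neither the number of items in part 2 nor its rating scale, so the size of any such effect cannot be calculated.
- *That a nurse who rightly lowers a rating would be counted as worse.* The factors are not listed, so nothing shows that any of them should be rated lower.
- *That the web-based questionnaire is the open-questions form and so has no pre-post score.* The article does not equate them. The rule calls the web-based questionnaire quantitative and scored at both times, which fits that form poorly. It might equally be the vehicle for the NEWS2 exercise.

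The reply does not remove the mismatch. Statistical Analysis says what is tested; Data Collection says what will be taken as effectiveness, and it does so without naming a part, a test or NEWS2. This is a stated rule that conflicts with the stated analysis, not a detail left to another document.

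**Conclusion.** The concern holds as a conflict of scope. The success rule is wider than the planned comparisons in one direction (the whole RRT survey and an unidentified questionnaire) and narrower in another (no NEWS2). Read literally, it would allow a rise in importance ratings to be reported as effectiveness with neither a planned test nor a gain in knowledge behind it.

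The exposure lies in how results are interpreted and reported. The paired tests, the minimum of 34 and the planned 50 are unaffected. The conclusion rests on two facts in the article: it states no direction of benefit for part 2, and it describes the web-based questionnaire nowhere outside the rule. It would weaken if the full protocol or the instrument's scoring guide fixed a direction for part 2 or identified the questionnaire. It does not rest on any assumption about item counts or a total score. Because the correction costs only wording, it should be made.

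**What to change.** 1. In Data Collection and Postintervention Assessment, limit the statement about effectiveness to the endpoints that Statistical Analysis compares: the RRT part 1 score, with its scoring direction fixed in advance, and NEWS2. Replace the reading of any increase with the result of the planned paired tests.
2. Identify the web-based questionnaire, for example by saying whether it is the NEWS2 exercise. Remove it from the rule only if it has no pre-post score; deleting it unexamined, or confining effectiveness to part 1, could drop NEWS2.
3. Report part 2 descriptively, in addition to its Cronbach's alpha, unless a direction of benefit is prespecified.

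The cost is a change of wording. No participants, procedures or tests are added, and the sample size stays as planned. The downside is that a shift in part 2 ratings could no longer be claimed as effectiveness.
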